#### Sample size calculations

4.1.2

All power calculations are conducted using software PASS 14.0.9 and R 4.3.1, unless otherwise indicated.

For testing the sensitivity, we expect the sensitivity to be 90% from the second test in each of the paired comparisons (reader 1 mpMRI), and assume a margin of 8% in defining noninferiority and an actual difference of 0%. We expect the percentage of probability of the first test giving a positive result while the second giving a negative result will be 5%. A sample size of 145 patients achieves at least 80% power at significance level 0.05. We plan to enroll 500 patients and expect that 30% will be diagnosed with csPCa, yielding 175 analyzable patients for the evaluation of sensitivity. Given the design of the trial, missing data are expected to be low (3%). Therefore, with the proposed sample size, we will have ample power in the above statistical tests.

For testing the specificity, we expect the specificity to be 40% from the second test in each of the paired comparisons, and assume a margin of 10% in defining noninferiority [42] and an actual difference of 0%. We expect the percentage of probability of the first test giving a negative result while the second giving a positive result will be 5%. Of 500 patients enrolled, 350 are expected to not be diagnosed with csPCa (either no biopsy due to low clinical/imaging risk or biopsy negative for csPCa), with a missing data rate of 3%. A sample size of 340 analyzable patients achieves at least 80% power at significance level 0.05.

For testing the noninferiority of the ROC curves associated with RSIrs and mpMRI, a preliminary study of 476 patients indicates that the AUC of the model with RSIrs is 0.747 (95% confidence interval [CI]: 0.7025–0.7884), while the AUC of the model with mpMRI is 0.767 (95% CI: 0.726–0.8085). With the proposed sample size, we will have at least 80% power in the noninferiority test with a margin of 8%. The power analysis is conducted with R 4.3.1 and package pROC.

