### Study population

2.3

We will acquire subject data from five sites: University of California San Diego (UCSD), University of California San Francisco (UCSF), Massachusetts General Brigham Hospital (MGB), Weill Cornell Medical College (Cornell), and the University of Cambridge, UK (Cambridge). Patients referred for prostate mpMRI at any of the five participating sites, with a clinical suspicion of PCa, and those who meet all the inclusion/exclusion criteria in Table 2 will be eligible for the trial. As a pragmatic study, eligibility criteria are broad to reflect the patient population currently referred for prostate MRI. We will include a total of 500 patients in the trial (100 from each of the five sites).

**Table 2 t0010:** Eligibility criteria

*Inclusion criteria*
1. 18 yr of age or older
2. Referred for mpMRI of the prostate for suspicion of prostate cancer
3. MRI is conducted using the standardized ART-Pro acquisition protocol
*Exclusion criteria*
1. Currently incarcerated
2. Previous diagnosis of prostate cancer
3. Active nonprostate tumor(s) in structures of the body near the prostate
4. Previous prostate surgery
5. History of hip implant
6. Metal implants or implanted devices in the body or other criteria that are deemed to require deviation from the usual acquisition protocol or scanning procedures

mpMRI = multiparametric MRI; MRI = magnetic resonance imaging.

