ART-Pro’s pragmatic design facilitates conduct of the study but also has some limitations. Biopsy decisions are made as per clinical routine and are not prescribed by the study, so biopsy may not be performed for some patients despite suspicious MRI. On the contrary, this reflects real-world practice. We expect that conducting the study at centers of excellence will mitigate the risk of nonstandard recommendations, and we have accounted for the possibility of patients declining a recommended biopsy in our power analysis. Clinical decisions for each patient are made based on the final recommendations of one radiologist (ART-Pro-1 reader 1). It is obviously not possible to have the same patient undergo two separate decisions, and our design allows for both reader 1 and reader 2 to influence the biopsy decision and biopsy targets. An alternative approach would be a randomized trial where patients are evaluated with only bpMRI, mpMRI, or RSIrs plus bpMRI. Such a randomized trial would suffer drawbacks of requiring many more patients (because of nonpaired statistical comparisons) and a considerable consenting effort that would inevitably slow accrual and introduce biases because some patient populations are less able to participate in research studies (eg, because of language barriers, complex wording of consent forms, burden of additional visits to complete consent, etc.). ART-Pro-2 has a retrospective design, meaning that the ART-Pro-2 radiologists do not influence biopsy decisions. They may, for example, identify additional lesions that were not targeted on biopsy. Given that each patient can have only one biopsy recommendation and the first biopsy procedure, we believe that the most ethical and most accurate approach is to have two expert radiologists at a center of excellence to influence biopsy recommendations that lead to the gold standard reference for the study’s primary outcome (presence of csPCa on biopsy).

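### The 175 analyzable csPCa patients for the sensitivity test should be about 145, so there is no surplus over the stated requirement of 145

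*Protocol article*

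**What the plan says.** The relevant statements in the protocol article are these.

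- Section 2.3 (Study population) fixes enrolment at 500, as 100 from each of five sites.
- Section 4.1.2 (Sample size calculations) gives the requirement for sensitivity: "A sample size of 145 patients achieves at least 80% power at significance level 0.05". The inputs are 90% sensitivity for reader 1 mpMRI, an 8% margin, no true difference, and a 5% chance that the first test is positive and the second negative.
- The same paragraph gives the expected yield: "We plan to enroll 500 patients and expect that 30% will be diagnosed with csPCa, yielding 175 analyzable patients for the evaluation of sensitivity". It then expects 3% missing data and concludes that power is ample.
- The next paragraph, on specificity, says: "Of 500 patients enrolled, 350 are expected to not be diagnosed with csPCa". After 3% missing it works with 340 analyzable patients.
- Section 4.1.1 makes the noninferiority tests one-sided, at significance level 0.05.
- Section 5 (Summary) adds: "we have accounted for the possibility of patients declining a recommended biopsy in our power analysis".

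**The concern.** The yield of 175 does not follow from the two numbers in its own sentence, and it cannot be squared with the specificity paragraph. It matters because the text draws a conclusion from it: 175 expected against 145 required looks like 30 spare csPCa patients, and the judgement that power is ample follows as a consequence. Detection of csPCa is the primary objective, and of the two accuracy tests sensitivity rests on the smaller group. Section 4.2 also refers back to this calculation when it claims the same power for each ART-Pro-2 experience level. A reader who relies on the 30-patient reserve would think the trial can absorb lower prevalence or more missing outcomes before falling below its stated requirement. It cannot.

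**Working it through.** **Inputs.** Enrolment 500 (Sections 2.3 and 4.1.2); csPCa 30%; missing 3%; required csPCa patients 145; margin 0.08; true difference 0; one discordant cell 0.05 (all Section 4.1.2); one-sided test at 0.05 (Section 4.1.1). With a true difference of 0 the other discordant cell is also 0.05, so total discordance is 0.10.

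**1. Trying to reproduce 175.**
- No loss: 500 × 0.30 = 150.
- 3% loss: 150 × 0.97 = 145.5.
- 3% applied as inflation: 150 / 0.97 = 154.6.
- None gives 175, but 500 × 0.35 = 175.

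**2. Cross-check with the specificity paragraph.**
- 500 − 350 = 150 with csPCa, which is 30%.
- 350 × 0.97 = 339.5, which matches the printed 340.
- As printed, the groups total 175 + 350 = 525, or 175 + 340 = 515 analyzable, from 500 patients.
- Working back from the requirement: 145 / 0.97 ≈ 150, and 150 / 0.30 = 500. Enrolment of 500 fits a requirement of 145 exactly, with nothing over.

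**3. Surplus over the requirement.** As printed, 175 − 145 = 30. Corrected, 145.5 − 145 ≈ 0. Reaching 175 analyzable patients at 30% and 3% would take 175 / (0.30 × 0.97) ≈ 602 enrolled.

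**4. Chance variation.** Suppose each patient independently has probability 0.30 × 0.97 = 0.291 of being an analyzable csPCa case. For a binomial with n = 500, P(fewer than 145) = 46% and P(175 or more) = 0.2%.

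**5. Power at the corrected count.** For the Wald form, power = Φ(0.08 / √(0.10/n) − 1.645).
- n = 145: 0.08 / 0.02626 = 3.046; Φ(1.401) = 91.9%.
- n = 175: 0.08 / 0.02390 = 3.347; Φ(1.702) = 95.6%.

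Exact enumeration of the discordant counts, one-sided 0.05:

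| Analyzable csPCa | Score test (restricted variance) | Wald | Wald, continuity-corrected |
|---|---|---|---|
| 115 | 81.8% | 86.0% | 79.0% |
| 130 | 86.1% | 88.4% | 83.9% |
| 145 | 88.6% | 91.2% | 87.7% |
| 175 | 93.6% | 94.9% | 92.8% |

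**6. Where 145 may come from.** At one-sided 0.05 the Wald formula needs only (1.645 + 0.842)² × 0.10 / 0.08² = 97 patients for 80% power, and the asymptotic score test needs 119. The exact score test at one-sided 0.025 gives 80.5% at 145, so that variant would explain the number. The article does not state that level for this test.

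**7. Lower prevalence.** 28% gives 500 × 0.28 × 0.97 ≈ 136 analyzable; 25% gives ≈ 121. Both are below the stated 145.

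**The case against.** The strongest reply is that the slip has little consequence. The corrected count still meets the stated 145, so the claim of at least 80% power survives, and so does enrolment of 500. At the stated alpha and discordance, 145 patients give about 89–92%, which can fairly be called ample against an 80% target. This stands: the number must change, but the adjective can stay if it rests on a stated power.

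Three stronger readings are tempting, and the article does not support them.

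- *The sensitivity test is underpowered.* Under the planned assumptions it is not. Even 115 patients give about 82–86% with the score or Wald test, and 79% only with a continuity correction. A shortfall below 145 would mean less than 80% power if the calculation was made at one-sided 0.025, but the stated level is 0.05.
- *The Summary's statement about declined biopsies is false.* The 30% refers to patients who will be diagnosed, which is an outcome after biopsy uptake and may already be net of refusals. The full power analysis is not shown. What can be said is that 3% missing is the only explicit allowance, and that the 350 is described as unbiopsied low-risk or biopsy-negative men, so patients who decline a recommended biopsy have no visible place.
- *Discordance between two different readers will exceed 5% and use up the power.* That is a separate question. It needs a figure the article does not give, and the multiplication error is not its cause.

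**Conclusion.** The figure of 175 is wrong on its own inputs. The expected number of analyzable csPCa patients is about 145, so 175 overstates it by 30 (30 / 145 ≈ 21%), and the surplus over the stated requirement is zero. On the planned assumptions the cost is about 4 to 5 percentage points of power (88.6% against 93.6% by the exact score test; 91.9% against 95.6% by the Wald formula), and the 80% claim holds. This rests on 30% being the intended prevalence, which the 350 and 340 confirm, and on 5% discordance in each direction with a one-sided 0.05 test. The allowance for declined biopsies is unclear, not shown to be wrong. Severity: should-fix.

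**What to change.** 1. In Section 4.1.2, replace 175 with about 145 (150 less 3%). If 35% was intended, change the 30% instead and make the specificity counts match: 500 × 0.65 = 325 without csPCa, and 325 × 0.97 ≈ 315 analyzable. In that case 175 is the count before missing data, and 175 × 0.97 ≈ 170 is the analyzable number.
2. Base the power statement on the power at 145 for the named test and alpha, with values at lower counts such as 130 and 115, and not on a surplus of 175 over 145.
3. Reconcile Section 5 with Section 4.1.2: state whether the 30% is already net of declined biopsies. If it is not, give the refusal rate assumed and the analyzable number that follows.

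The cost is wording in the protocol and any analysis plan. No extra patients and no change of design are needed, though the printed yield becomes less favourable.

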### Analyses for ART-Pro-2

4.2

Statistical analyses for ART-Pro-2 will be analogous to those described for ART-Pro-1. In ART-Pro-2, each radiologist will give sequential reports on each assigned patient case, that is, either (1) bpMRI and (2) mpMRI or (3) RSIrs plus T2W axial, (4) RSIrs plus bpMRI, and (5) RSIrs plus mpMRI. We will compare each approach (1 and 3–5) to mpMRI in an analogous manner to that in ART-Pro-1 using McNemar’s test and AUCs. These analyses will be performed within each stratum of ESUR radiologist expertise, testing for noninferiority compared with mpMRI PI-RADS for ESUR-defined experts (essentially a validation of ART-Pro-1), radiologists with basic prostate MRI proficiency, and novices. In terms of statistical power, each of these ART-Pro-2 subgroups will have the same statistical power as the primary and key secondary analyses of ART-Pro-1.

Additionally, we will estimate the effect of radiologist expertise for each approach (1–5) in linear mixed-effect models that utilize all the data from ART-Pro-2. Models will take the following form:csPCastatusscore+experience+(1|patient)+(1|radiologist)

Here, csPCa status is whether the patient was diagnosed with csPCa (binary), score is the PI-RADS or Likert score assigned, and experience is a categorical variable for ESUR/ESUI level of experience. Importance of radiologist experience within each approach (1–5) will be estimated by the parameter estimates for ESUR/ESUI basic proficiency and ESUR/ESUI novice levels, compared with a reference of ESUR/ESUI experts.

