#### RSIrs plus mpMRI patient cases

3.7.2

For RSIrs plus mpMRI patient cases, the radiologist will first be presented with only RSIrs maps and axial T2W images. The radiologist will complete a REDCap report based only on images from these two series. As PI-RADS does not apply to RSIrs plus axial T2W images, these reports will use the 5-point Likert scale used in the PROMIS trial: highly unlikely (1), unlikely (2), equivocal (3), likely (4), or highly likely (5). The radiologist will then proceed to review the full bpMRI image set (ie, adding conventional DWI and ADC) and will complete a second REDCap report according to PI-RADS v2.1 guidelines. Finally, the radiologist will review DCE images and complete a third REDCap report for mpMRI according to PI-RADS v2.1. In each report, the radiologist will provide an estimate of the probability of csPCa per lesion and per patient.

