#### Statistical analysis plan for primary and key secondary objectives

4.1.1

An exploratory data analysis will be conducted, and visualization tools, including the scatterplot, boxplot, and histogram, will be used to examine the data and potential missingness [39]. For all tests below, the significance level of 0.05 will be used in the statistical testing. All analyses will be conducted using software R 4.3.1.

For examining the noninferiority of bpMRI versus mpMRI for the detection of csPCa, we will conduct one-sided noninferiority tests of correlated proportions, to examine the sensitivity and specificity of the following paired readings: reader 1 bpMRI versus reader 1 mpMRI and reader 2 bpMRI versus reader 1 mpMRI. For both paired comparisons, the outcome of each reading for each patient is the binary result of positive or negative MRI. A McNemar's test will be used to test the null hypothesis that the differences in the probabilities (% of second test minus % of the first test) of positive MRI (for testing on sensitivity) and negative MRI (for testing on specificity) from the two readings in the paired comparison are larger than the predetermined noninferiority margins [40]. The *p* values will be reported for all tests.

For examining the noninferiority of RSIrs versus mpMRI, we will compare the areas under the receiver operating characteristic (ROC) curve (AUCs) of using RSIrs (continuous variable) to predict the binary outcome of csPCa versus using mpMRI (ordinal categorical variable; treat like continuous variable) to predict the outcome [41]. A noninferiority test will be conducted to compare the two ROC curves associated with the two predictors at significance level 0.05.

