## Summary

5

Prostate mpMRI improves the diagnostic pathway for PCa by increasing the detection of csPCa while also avoiding unnecessary biopsies. The major limitations of mpMRI are the need for IV contrast and its dependence on user expertise. The ART-Pro trial aims to test whether IV contrast can be avoided in the setting of standardized, state-of-the-art image acquisition, with or without addition of a quantitative imaging biomarker, RSIrs. Critically, ART-Pro will study whether novel technology can help nonexpert radiologists achieve performance comparable with expert radiologists, even without the use of IV contrast. In addition, unlike other studies evaluating mpMRI and bpMRI for csPCa detection, ART-Pro employs fully standardized image acquisition protocols across multiple centers. Test characteristics of RSIrs will additionally be evaluated as a standalone, quantitative biomarker. The primary endpoint of ART-Pro is biopsy-confirmed csPCa. A key secondary endpoint is unnecessary biopsies (ie, any biopsy resulting in no cancer or only GG 1).

ART-Pro is being conducted in two linked stages. ART-Pro-1 includes expert readers at five centers of excellence and will yield a carefully curated dataset under ideal conditions. ART-Pro-1 will answer several key questions: (1) Can IV contrast be avoided when expert radiologists are available? (2) Does the use of RSIrs facilitate omission of IV contrast? (3) How does performance of RSIrs alone (as an objective quantitative biomarker) compare with expert bpMRI and mpMRI interpretation in a multicenter study? ART-Pro-2 will leverage the carefully curated dataset from ART-Pro-1 to investigate the impact of IV contrast and RSIrs maps, respectively, on the accuracy of nonexpert radiologists. Since two of the drawbacks to prostate mpMRI (variable interpretation of results and false-positive findings) are exacerbated in nonexpert radiologists, investigating these prostate MRI techniques in nonexperts through ART-Pro-2 will be invaluable for determining the utility of the techniques.

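### RSIrs plus full mpMRI (approach 5) is tested against mpMRI only for noninferiority, so that test cannot establish a gain from adding RSIrs

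*Protocol article*

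**What the plan says.** Section 4.2 numbers five reports: (1) bpMRI, (2) mpMRI, (3) RSIrs plus axial T2W, (4) RSIrs plus bpMRI and (5) RSIrs plus mpMRI. It then states: "We will compare each approach (1 and 3–5) to mpMRI in an analogous manner to that in ART-Pro-1". The hypothesis is named in the next sentence, "testing for noninferiority compared with mpMRI PI-RADS for ESUR-defined experts", which goes on to list the basic and novice strata.

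Section 3.7.2 shows what approach 5 is. After the RSIrs-plus-T2W and RSIrs-plus-bpMRI reports, "the radiologist will review DCE images and complete a third REDCap report for mpMRI according to PI-RADS v2.1". The reader therefore has everything in approach 2 plus the RSIrs maps.

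The Summary gives the purpose of ART-Pro-2 as "to investigate the impact of IV contrast and RSIrs maps, respectively, on the accuracy of nonexpert radiologists". The Introduction and section 2.1 say the same in other words.

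The rules carried over from ART-Pro-1 are in sections 4.1.1 and 4.1.2: "we will conduct one-sided noninferiority tests of correlated proportions, to examine the sensitivity and specificity of the following paired readings"; "the significance level of 0.05 will be used in the statistical testing"; and for sensitivity "we expect the sensitivity to be 90% from the second test in each of the paired comparisons" and "assume a margin of 8% in defining noninferiority and an actual difference of 0". The specificity inputs are 40%, a 10-point margin and a true difference of 0. Section 4.2 claims the same power for each ART-Pro-2 expertise stratum.

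**The concern.** Noninferiority accepts a bounded loss of accuracy in return for some other benefit. That suits approaches 1, 3 and 4, which do without contrast. Approach 5 does without nothing, so the natural question is whether accuracy improves.

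Among the listed comparisons with mpMRI, approach 5 versus approach 2 is the only one that adds RSIrs without removing a sequence. In approaches 3 and 4 the effect of RSIrs is mixed with the effect of losing contrast. The plan's power is set at a true difference of 0, and for an add-on that is exactly the case in which RSIrs does nothing. The claimed power of at least 80% is then also a chance of at least 80% that an ineffective add-on passes. A pass would say little about RSIrs, and a real gain in basic or novice readers would have no planned test to establish it.

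**Working it through.** **Inputs (sections 4.1.1 and 4.1.2).** One-sided alpha 0.05. Sensitivity: margin Δ = 0.08, n = 145, 5% discordance in one direction; with true difference 0 this is 5% each way, so total d = 0.10. Specificity: Δ = 0.10, n = 340, d = 0.10 likewise.

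**Method.** Let b be the patients classed correctly by approach 5 only, and c those classed correctly by mpMRI only. The main results are exact power for the paired score test, Z = (b − c + nΔ) / √[n(2q − Δ − Δ²)], where q is the estimate of the c-cell probability restricted to a true difference of −Δ. The Wald approximation Φ(Δ/√(d/n) − 1.645) is a hand check.

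**The plan's own figure.** At n = 145 the score test has power 0.805 at one-sided 0.025 and 0.886 at one-sided 0.05. Both agree with the stated power of at least 80%.

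**Chance of passing when RSIrs has no effect, plan's inputs**
- Sensitivity: Wald 0.08/√(0.10/145) = 3.046; 3.046 − 1.645 = 1.401; Φ = 0.919. Score test **0.886**. It is 0.902 at n = 150 (30% of 500) and 0.936 at the stated 175.
- Specificity: 0.10/√(0.10/340) = 5.831; Φ(4.186) **> 0.999**.

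**Different readers.** Section 3.7 has each case read by different radiologists with and without RSIrs, so discordance may exceed 10%. Assumption for the upper end: independent errors, giving d = 2 × 0.9 × 0.1 = 0.18 and d = 2 × 0.4 × 0.6 = 0.48.
- Sensitivity: 0.08/√(0.18/145) = 2.271; Φ(0.626) = 0.734. Score test **0.72**.
- Specificity: 0.10/√(0.48/340) = 2.661; Φ(1.016) = 0.845. Score test **0.85**.

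**True 2-point loss of sensitivity, n = 145.**
- d = 0.10: Wald 0.06/√(0.0996/145) = 2.289; Φ(0.644) = 0.740. Score test **0.68**.
- d = 0.18: Wald 0.06/√(0.1796/145) = 1.705; Φ(0.060) = 0.524. Score test **0.51**.

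**Superiority instead (two-sided 0.05, McNemar).** With no effect, the chance of declaring a gain is about 2.5%.

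| Gain in sensitivity, n = 145 | d = 0.10 | d = 0.18 |
|---|---|---|
| 8 points | 0.92 | 0.65 |
| 5 points | 0.48 | 0.30 |

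The d = 0.18 column needs mpMRI sensitivity below 90%, because cases gained cannot exceed cases mpMRI misses. An 8-point gain there means 13% gained and 5% lost, so mpMRI sensitivity of at most 87%. A 5-point gain means 11.5% gained and 6.5% lost, so at most 88.5%.

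For a 5-point gain in specificity at n = 340, power is 0.86 at d = 0.10. At d = 0.48 it is about Φ(0.05/√(0.4775/340) − 1.96) = Φ(−0.63) = 0.27.

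**The case against.** **No listed objective covers this contrast.** Table 1 has none for RSIrs added to full mpMRI; objective 10 concerns RSIrs and bpMRI. The hypotheses in section 4 concern bpMRI, RSIrs plus bpMRI and stand-alone RSIrs. This stands, and it limits the weight of the point. A reader might infer that ART-Pro-2 as a whole cannot show what RSIrs does. The documents do not support that: approaches 3 and 4 carry the contrast-free aim, and noninferiority is apt for them.

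**Other analyses exist.** Section 4.3 compares approaches 1–5 by AIC, and plans ROC curves with bootstrap intervals for the probability estimates. So approach 5 is not left to one test. But the AIC comparison has no test, margin or decision rule, and no superiority hypothesis for 5 versus 2 is stated.

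**A gain might be reported anyway.** Section 4.1.1 promises p values and does not exclude estimates or intervals. It would therefore be too strong to say that a gain would be hidden. The narrower point remains: the hypothesis the article assigns to approach 5 cannot establish one.

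**The pass rates merely restate power.** Any noninferiority test powered at zero difference behaves this way, and checking that RSIrs does not harm reading is legitimate. Both are true, which is why noninferiority can stay as a first step. The pass rate also falls in harsher settings: about 0.61 with independent readers and both endpoints required (0.45 at one-sided 0.025), and about 0.47 for sensitivity alone if novices had 75% sensitivity with independent errors. The article does not say that both endpoints are required together.

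**Scan time.** A reader might add that approach 5 imposes extra scanning. Sections 3.2 and 4.2 do not support that as a general charge: at the four US sites the two short-TE RSI scans are already clinical.

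**Conclusion.** The point holds for one comparison only, approach 5 against approach 2. Section 4.2 expressly assigns it a noninferiority test although nothing is omitted, so this is a stated hypothesis that does not fit, not a detail left for an unseen analysis plan.

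An add-on with no effect passes about 89% of the time for sensitivity and over 99.9% for specificity at the plan's inputs, or about 72% and 85% if readers err independently. With a true 2-point sensitivity loss it passes about 51–68%. The independent-error figures rest on an assumed discordance that the article does not give; the plan-input figures rest only on its own numbers. Because the comparison is ancillary to Table 1, this is a worthwhile improvement and not a threat to the primary objective.

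**What to change.** In section 4.2, for approach 5 versus approach 2, keep noninferiority as the first step and add a superiority test on the same paired difference. Report a 95% confidence interval for the difference in sensitivity, specificity and AUC within each experience level. Leave approaches 1, 3 and 4 as noninferiority comparisons. Fix this before the ART-Pro-2 reads are analysed.

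The cost is a sentence or two; no new patients or reads. There are two downsides to state openly. The fixed order costs no alpha only within each comparison, and there are three metrics in three strata, so these results should be labelled secondary. Superiority power is also modest for sensitivity at n = 145: about 65–92% for an 8-point gain and 30–48% for a 5-point gain, depending on discordance.

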### MRI interpretation in ART-Pro-2

3.7

ART-Pro-2 will be conducted retrospectively and will not impact patient care. Radiologists will be categorized by level of experience for prostate MRI based on the joint European Society of Urogenital Radiologists (ESUR) and the EAU Section of Urological Imaging (ESUI) criteria: novice prostate radiologists defined as having read <400 cases, basic prostate radiologists defined as having read ≥400 and <1000 cases, and expert prostate radiologists defined as having read ≥1000 cases [11]. The design of ART-Pro-2 in evaluating nonexpert readers retrospectively allows for “locking” of reader experience level, whereas if evaluated over the ART-Pro-1 trial period, readers could change (by criteria) from being novice to basic and/or expert. Each radiologist will be provided a list of 100 patient cases to review, 50 with mpMRI and 50 with RSIrs plus mpMRI. Case lists will be generated as random permutations of cases while requiring that (1) no radiologist be assigned cases from the institution where he/she works (to ensure that the radiologist has not seen the cases before), (2) each patient case is assigned to at least three radiologists as mpMRI (one from each of the experience levels), and (3) each patient case is assigned to at least three (different) radiologists (one from each of the experience levels) as RSIrs plus mpMRI. Thus, each patient case will be reviewed by six radiologists (two from each of the experience levels). Image sets will be provided as sessions using the MIM Zero Footprint platform (MIM Software, Cleveland, OH, USA) to facilitate individual work lists and presentation of image subsets.

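### ART-Pro-2 tests noninferiority within each expertise level with no reader term, although about 10 readers supply all the pairs. If the technique difference varies between readers, variance is understated and the same-power claim fails.

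*Protocol article*

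**What the plan says.** The article fixes the reading design in sections 2.3 and 3.7:

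- Patients: "We will include a total of 500 patients in the trial (100 from each of the five sites".
- Reader load: "Each radiologist will be provided a list of 100 patient cases to review, 50 with mpMRI and 50 with RSIrs plus mpMRI".
- Reads per case: "each patient case will be reviewed by six radiologists (two from each of the experience levels". Each level therefore supplies one mpMRI read and one RSIrs plus mpMRI read of every case, by different radiologists.

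Section 4.2 fixes the test: "We will compare each approach (1 and 3–5) to mpMRI in an analogous manner to that in ART-Pro-1 using McNemar’s test and AUCs". It adds: "These analyses will be performed within each stratum of ESUR radiologist expertise". Section 4.1.1 defines the ART-Pro-1 method that this copies: "we will conduct one-sided noninferiority tests of correlated proportions", where "the outcome of each reading for each patient is the binary result of positive or negative MRI". It also sets the level: "For all tests below, the significance level of 0.05 will be used in the statistical testing".

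Section 4.2 then states that each expertise subgroup has the same power as the primary and key secondary ART-Pro-1 analyses. A random radiologist effect appears only in a separate mixed model. That model has csPCa status as its outcome and estimates the effect of experience.

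**The concern.** A McNemar-type test on patient-level pairs treats every pair as independent. In ART-Pro-2 the pairs come in blocks: all cases read by one radiologist share whatever that radiologist gains or loses from a technique. With about 10 readers per level, this shared component does not average out as it would over 145 or 340 independent pairs.

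The nonexpert comparison of bpMRI with mpMRI is part of the primary objective in Table 1, and the Summary looks ahead to wide implementation. The inference is therefore to novice and basic radiologists in general, so reader variance belongs in the test. Leaving it out makes intervals too narrow, raises the chance of a false noninferiority claim and overstates power. The mixed model does not repair this, because it does not test noninferiority.

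**Working it through.** **Readers per level.** Each level reads all 500 cases once as mpMRI, at 50 per reader: 500 / 50 = 10. The same 10 readers cover the RSIrs plus mpMRI reads. Check: 500 × 6 / 100 = 30 readers over three levels.

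**Pairs per test.** No test uses all 500 pairs. Sensitivity: 30% of 500 = 150, less 3% missing = 145.5. Specificity: 350, less 3% = 339.5. I use 145 and 340, the sizes named in section 4.1.2, so 14.5 and 34 pairs per reader.

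**The plan's own power.** Inputs from section 4.1.2: margins 8% and 10%, true difference 0, 5% discordance in one direction and hence 10% in total. With independent pairs, power = Φ(margin / √(0.10/n) − 1.645).

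- Sensitivity: √(0.10/145) = 0.0263; 0.08/0.0263 = 3.05; Φ(1.40) = 91.9%. A score test gives 88% by simulation.
- Specificity: about 100%.

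The stated figure of at least 80% is reproduced, but only for independent pairs.

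**Adding reader variance.** Let τ be the between-reader SD of the true bpMRI minus mpMRI difference. The documents give no value, so τ is an assumption. Design effect = 1 + (m − 1) × τ²/V, where m is pairs per reader and V is the variance of one pair difference.

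*Alpha at the margin.* V = 0.05 + 0.13 − 0.08² = 0.1736 for sensitivity and 0.05 + 0.15 − 0.10² = 0.19 for specificity. Actual alpha = 1 − Φ(1.645/√design effect). Example, specificity at τ = 5 points: 1 + 33 × 0.0025/0.19 = 1.43, so alpha = 1 − Φ(1.37) = 0.085. The score-test columns come from simulating 10 readers who each make both reads of a pair, with the true difference at the margin and 5% discordance in the gain direction.

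| τ (points) | Sensitivity, formula | Sensitivity, score test | Specificity, formula | Specificity, score test |
|---|---|---|---|---|
| 0 | 0.050 | about 5% | 0.050 | about 5% |
| 2-3.5 | 0.056 (τ = 3) | 5-6% | 0.063 (τ = 3) | 6-7% (τ = 3.5) |
| 5 | 0.066 | about 7% | 0.085 | 8-9% |
| 8 | 0.089 | about 9% | 0.129 | 12-14% |

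*Power at true difference 0.* V = 0.10. For sensitivity the design effect is 1 + 13.5 × τ²/0.10:

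- τ = 5 points: 1.34; SE = √(0.1338/145) = 0.0304; Φ(2.63 − 1.645) = 84%.
- τ = 8 points: 1.86; SE = √(0.1864/145) = 0.0359; Φ(2.23 − 1.645) = 72%.

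Power crosses 80% near τ = 6 points (design effect 1.49). Specificity power stays at 88% or more up to τ = 10 points. These figures use the normal quantile. A t reference on 9 df (critical value 1.833; noncentrality 3.05, 2.63 and 2.23) gives about 88%, 78% and 66% for sensitivity at τ = 0, 5 and 8 points.

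**Approaches 3-5 versus mpMRI.** Here the two reads of a case come from different radiologists. In a probit simulation with a Wald test, reader main effects alone (SD 0.5) gave alpha of 0.065 for sensitivity and 0.038 for specificity. Adding reader-by-technique SDs of 0.2-0.3 gave 0.09-0.11 and 0.12-0.18. Again it is variation in the technique effect that drives the inflation.

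**The case against.** The strongest reply is that the documents show no such variation. The Introduction says that results differ widely between radiologists, but that concerns the level of performance, not the bpMRI minus mpMRI difference. In that comparison the same radiologist reads the same case in sequence, so much of the level variation cancels. With τ = 0 the test holds about 5%. With a score test, sensitivity barely moves at 2-3.5 points. This stands, and it limits the size of the point. It does not remove it: the Introduction also reports that contrast images help nonexperts find regions they might otherwise miss, which is a reason to expect the technique effect to depend on the reader.

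A second reply is that an article may leave the variance estimator to an analysis plan. That would hold if the method were unstated. Here the test is named, the unit is the patient pair, and a power claim is made on that basis.

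Third, the count of 10 is inferred, since section 3.7 first says at least three radiologists per mode. The same section then concludes that six radiologists read each case, which gives 10 per level.

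Fourth, a simple reader-clustered variance is no complete remedy. For same-reader pairs, a t reference on 9 df gave alpha of about 5-6.5% up to 5 points and about 6-8% at 8 points, depending on the shape assumed for reader effects. For approaches 3-5 a pair belongs to two readers, so one-way clustering is not well defined. The fix allows for this.

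**Conclusion.** The point holds in a conditional form. Section 4.2 commits to a test that treats pairs as independent when about 10 readers per level supply them. If the technique difference varies between readers, and the target is novice and basic radiologists beyond those sampled, the variance is understated. For bpMRI versus mpMRI the effect is small for sensitivity at modest τ (5-6% at 2-3.5 points, 9% at 8). It is larger for specificity (6-7% at 3.5 points, 8-9% at 5, 12-14% at 8). The same-power statement fails whenever τ exceeds zero, and sensitivity power drops below 80% from about 6 points.

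A reader might infer that ART-Pro-2 is bound to declare noninferiority too often, or that ordinary differences in reader skill are enough to cause this. The documents support neither: they give no between-reader SD, alpha is about 5% when τ is 0, and level differences largely cancel. Nor is any single test based on 500 pairs. The correction is worth making before the reads are analysed, but it does not invalidate the design.

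**What to change.** In section 4.2:

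1. Base the noninferiority decisions within each level, including the AUC comparisons, on a multi-reader multi-case analysis with readers and cases as random.
2. For bpMRI versus mpMRI by the same reader, a reader-clustered paired difference with a t reference on (readers − 1) df is an acceptable alternative. For approaches 3-5 use the multi-reader multi-case analysis, or two-way clustering on both readers of a pair.
3. Replace the same-power sentence with power recomputed for about 10 readers per level, over a stated range of reader-by-technique SD.

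The cost is analysis code and a revised power statement, with no extra readers or reads. The downside is wider intervals and lower stated ART-Pro-2 power, most visibly for sensitivity. If the recomputed power were judged too low, raising it would be a separate decision about reader numbers.
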